## Abstract

**Background:**

Falls in older people are a major public health problem, with at least one in three people aged over 65 years falling each year. There is increasing evidence that foot problems and inappropriate footwear increase the risk of falls, however no studies have been undertaken to determine whether modifying these risk factors decreases the risk of falling. This article describes the design of a randomised trial to evaluate the efficacy of a multifaceted podiatry intervention to reduce foot pain, improve balance, and reduce falls in older people.

**Methods:**

Three hundred community-dwelling men and women aged 65 years and over with current foot pain and an increased risk of falling will be randomly allocated to a control or intervention group. The "usual cae" control group will receive routine podiatry (i.e. nail care and callus debridement). The intervention group will receive usual care plus a multifaceted podiatry intervention consisting of: (i) prefabricated insoles customised to accommodate plantar lesions; (ii) footwear advice and assistance with the purchase of new footwear if current footwear is inappropriate; (iii) a home-based exercise program to strengthen foot and ankle muscles; and (iv) a falls prevention education booklet. Primary outcome measures will be the number of fallers, number of multiple fallers and the falls rate recorded by a falls diary over a 12 month period. Secondary outcome measures assessed six months after baseline will include the Medical Outcomes Study Short Form 12 (SF-12), the Manchester Foot Pain and Disability Index, the Falls Efficacy Scale International, and a series of balance and functional tests. Data will be analysed using the intention to treat principle.

**Discussion:**

This study is the first randomised trial to evaluate the efficacy of podiatry in improving balance and preventing falls. The trial has been pragmatically designed to ensure that the findings can be generalised to clinical practice. If found to be effective, the multifaceted podiatry intervention will be a unique addition to common falls prevention strategies already in use.

**Trial registration:**

Australian New Zealand Clinical Trials Registry: ACTRN12608000065392

## Background

Falls in older people are a major public health problem, with one in three people aged 65 and over falling each year [1,2]. One-quarter to one-half of all falls among community-dwellers cause some injury, 10–15% of falls are associated with serious injury, 2–6% with fractures and around 1% with hip fractures [3]. The most commonly self-reported injuries include superficial cuts and abrasions, bruises and sprains. The most common injuries that require hospitalisation comprise femoral neck fractures, other fractures of the leg, fractures of radius, ulna and humerus and fractures of the neck and trunk [3]. Falls are the leading cause of injury-related hospital admissions in older people, accounting for 4% of all hospital admissions in this age-group [4].

It is now well recognised that falls result from an interaction between environmental hazards and a broad array of physiologic risk factors, including impaired vision, reduced muscle strength, diminished peripheral sensation and slow reaction time [5]. However, one potentially significant falls risk factor that has only recently been explored is foot impairment. Foot problems affect one in three community dwelling people over the age of 65 years [6,7] and are associated with reduced walking speed and difficulty performing activities of daily living [8-10]. A recent prospective study of 176 older people indicated that ankle flexibility, toe plantarflexor strength and plantar sensation were significant and independent predictors of balance and functional test performance, explaining up to 59% of the variance in these test scores [11]. A 12-month follow-up of this cohort confirmed that these factors, in addition to foot pain, were significant independent predictors of falls [12].

In addition to foot pain and impairment, inappropriate footwear may also play a role in increasing falls risk. A number of studies have assessed footwear in older people who have fallen, and the evidence indicates going barefoot or wearing stockings increases the risk of a fall, as does an increased heel height and smaller sole contact area [13,14]. A number of other studies have investigated the main features of a shoe thought to affect balance, with heel height [15], heel collar height [16], fixation (method used to attach the shoe to the foot) [17] and the slip resistance properties of the sole [18] all being associated. This evidence suggests there is a relationship between footwear and falls and that wearing appropriate footwear may reduce the risk of falls.

Given the emerging evidence that foot problems and inappropriate footwear increase the risk of falls, it has been suggested that podiatry may have a role to play in falls prevention, with several guidelines recommending that older people have their feet and footwear examined by a podiatrist [19-21]. In light of this, it is surprising to find that podiatry has been largely overlooked in falls intervention trials. Only one intervention study has included foot and footwear assessment as part of a nurse-led multifactorial approach to falls. In this study, the assessments were conducted by trained nurses who referred to a relevant specialist depending on the problem found, which in the case of foot problems or inappropriate footwear was a podiatrist [22]. Furthermore, podiatry currently plays a relatively minor role in multidisciplinary falls clinics, with two recent surveys indicating that only 4 out of 25 Australian falls clinics [23] and 1 out of 105 National Health Service trusts in London involved in falls prevention activities [24] utilised podiatrists.

While falls prevention guidelines have recommended that older people have their feet and footwear examined by a podiatrist, these guidelines do not specify the assessment or intervention activities to be undertaken. This may be due to the limited amount of evidence from clinical trials regarding the efficacy of podiatry treatment in reducing pain, improving mobility and decreasing the risk of falls. Although callus debridement and accommodative padding have been shown to reduce weightbearing pressures under the foot [25-27] and reduce pain [28-30], a small pilot study by Balanowski and Flynn is the only study to assess any form of podiatric treatment in relation to functional ability and balance in older people [28]. Functional and static balance tests were conducted before and seven days after scalpel debridement of painful plantar keratoses in 19 older people. Follow-up tests indicated significant improvements in functional ability, however the small sample size, lack of a control group and short follow-up time indicate that further work in this area is required.

An additional factor that has been largely overlooked in the literature is the role of foot and ankle stretching and strengthening in improving balance and decreasing the risk of falls. Although muscle weakness has been shown to be an important risk factor for falls [31] and exercise is recommended in recent evidence-based guidelines for falls prevention [32-34], only one study has demonstrated that increasing toe plantarflexor strength can improve balance ability [35]. Similarly, while reduced ankle flexibility is associated with falls [12], few studies have directly evaluated the potential benefits of ankle stretching and strengthening in improving balance even though it has been shown to improve with stretching [36] and water exercise [37].

Given the detrimental effects of foot problems and inappropriate footwear and the paucity of studies undertaken to ascertain the efficacy of podiatry treatment in falls prevention, the aims of this project are to determine the effectiveness of a multifaceted podiatry intervention in (i) reducing disabling foot pain, (ii) enhancing balance and mobility, and (iii) preventing falls in older people.

## Methods

### Design

This study is a parallel-group randomised trial with a one-year follow-up (Figure 1). The Human Ethics Committee of La Trobe University Human has approved the trail and all participants will give written informed consent. Participants will be randomly allocated to either a "usual care" control group or the "multifaceted podiatry" intervention group. Permuted block randomisation will be undertaken using an interactive voice response telephone service provided by the National Health and Medical Research Council Clinical Trials Centre at the University of Sydney. Assessors will be blinded to group allocation but due to the nature of the trial, the participants will not be blinded to group allocation.

**Figure 1 F1:**
[figure not shown]
Design of study.

### Participants

Community dwelling men and women aged 65 years and over will be recruited by a mail-out letter from two databases: (i) people who are currently accessing podiatry services at the La Trobe University Health Sciences Clinic, Bundoora, Victoria, Australia and (ii) people who are currently accessing podiatry services at the Bundoora Extended Care Centre, Victoria, Australia as well as from advertisements placed in seniors newspapers and websites. Respondents will be initially screened by telephone to ensure they are able to walk household distances without the use of a walking aid and are able to read and speak basic English. Individuals who meet the initial screening criteria will then be invited to be assessed for eligibility.

To be included in the study, participants must meet the following inclusion criteria:

(i) an elevated risk of falling, defined as either a history of a fall in the previous 12 months, a score of > 1 on the short Physiological Profile Assessment (PPA) [5] or performance on the alternate stepping test (the time taken to alternately place each foot on a 19 cm high step eight times) of > 10 seconds [38];

(ii) self-reported disabling foot pain (defined as people who have had foot pain lasting for at least a day within the last month and a positive response to at least one item on the Manchester Foot Pain and Disability Index [39]);

(iii) cognitively intact (defined as a score of ≥ 7 on the Short Portable Mental Status Questionnaire [40]).

Participants will be excluded if they have Parkinson's disease (or other neurodegenerative disorders) or lower limb amputation (including partial foot amputation).

### Control group

The control group will be asked to continue whatever podiatry treatment they currently receive for the 12 months of the study. All participants will be offered basic podiatry treatment free of charge in the La Trobe University Health Sciences clinic for the 12 months of the study regardless of whether they are current patients of the clinic. This will typically include toenail maintenance and scalpel debridement of hyperkeratotic lesions (corns and calluses). This intervention is consistent with the usual ongoing "maintenance" care that is provided to older people attending public sector podiatry services (such as community health centres, outpatient podiatry clinics and Department of Veterans' Affairs subsidised private podiatry).

### Intervention group

The intervention group will also be asked to continue whatever podiatry treatment they currently receive for the 12 months of the study and all participants will be offered basic podiatry treatment free of charge in the La Trobe University Health Sciences clinic for the 12 months of the study regardless of whether they are current patients of the clinic. In addition, they will receive a multifaceted podiatry intervention consisting of:

(i) *Footwear advice and provision*: participants' outdoor footwear will be assessed using a footwear assessment form for which the component variables have been shown to have good intra-rater reliability (intra-rater kappa 0.62 – 1.0) [41]. Participants will be deemed to have inappropriate footwear if the heel height is greater than 4.5 cm or the shoe has any two of the following; no fixation, no heel counter or the heel counter can be depressed to greater than 45°, the tread pattern of the sole is fully worn or manufactured with a smooth sole, or the shoe heel width is narrower than the participant's heel width by greater than or equal to 20%. Participants with inappropriate footwear will be counselled regarding the specific hazardous footwear feature/s identified, and will be provided with a handout on what constitutes a safe shoe. They will then be given the contact details of an extra-depth and medical grade footwear retailer and will be asked to purchase a more appropriate pair of shoes. Their purchase of footwear will be assisted by the provision of an AUD$100 voucher.

(ii) *Foot orthoses*: Prefabricated insoles (Formthotics™, Foot Science International Ltd, Christchurch, New Zealand) manufactured from a thermoformable cross-linked closed cell polyethylene foam will be shaped to fit the participant's foot (Figure 2). The orthoses will then be appropriately customised using 3 mm thick PPT urethane to redistribute pressure away from plantar lesions (Figure 3).

**Figure 2 F2:**
[figure not shown]
Prefabricated orthoses (Formthotics(tm), Foot Science International Ltd, Christchurch, New Zealand) used in the study.

**Figure 3 F3:**
[figure not shown]
Examples of insole designs to redistribute pressure away from plantar hyperkeratotic lesions to be incorporated into the foot orthoses used in the study.

(iii) *Home-based exercise program*: participants will be provided with instructions and practical demonstrations at the baseline assessment to allow them to undertake a 30 minute home-based exercise program aimed at stretching and strengthening the muscles of the foot and ankle. Strength will be assessed at baseline and appropriate intensity prescribed. A summary of the individual exercises is provided in Table 1. All necessary equipment to undertake the exercise program, including an Archxerciser™ (Elginex Corporation, Lombard, Illonois, USA) (Figure 4) will be provided. Participants will also be given an illustrated explanatory booklet of each exercise, a DVD demonstrating the exercises and an exercise diary to be returned monthly to the researchers. The program will be performed three times per week for six months, and participants will be contacted at one, four, twelve and twenty weeks by telephone to promote adherence to the program.

**Table 1 T1:** Description of specific exercises.

**Name**	**Description**	**Dosage**	**Increments**
Ankle range of motion	Sitting with leg extended. Rotate foot in clockwise direction then anti-clockwise	1 × 10 repetitions for each foot in each direction	None
Ankle dorsiflexion strength	Sitting, hip and ankle at 90°. Dorsiflex both feet to end range of motion and hold.	Hold feet in dorsiflexion for 3 × 10 seconds	Increase repetitions up to maximum of 10
Ankle inversion strength	Sitting, hip and ankle at 90°. Invert foot against resistive exercise band anchored by chair leg	3 × 10 repetitions for each foot	Increase resistance strength of resistive exercise band
Ankle eversion strength	Sitting, hip and ankle at 90°. Evert foot against resistive exercise band anchored by chair leg	3 × 10 repetitions for each foot	Increase resistance strength of resistive exercise band
Ankle plantarflexion strength	From standing, rise up on to toes of both feet and back down	3 × 10 repetitions	Increase repetitions up to maximum of 50.
Gastrocnemius stretch	Standing stretch leaning against wall. Stretch leg is extended with knee locked. Support leg forward with knee bent	Hold stretch for 3 × 20 seconds on each leg	Increase forward lean to increase stretch as required
Toe plantarflexion strength	Heel on plate of Archxerciser™. Toes over spring loaded toebar. Retract bar	3 × 10 repetitions for each foot	Increase distance bar is retracted
Toe plantarflexion strength	Pick up 25 mm stones and place in box.	Pick up 2 × 20 stones for each foot.	None
Adductor hallucis stretch	Elastic band around both hallux. Move feet apart	3 × 20 seconds	None

All exercises to be performed 3 times a week for 6 months from baseline to follow up assessment.

**Figure 4 F4:**
[figure not shown]
The Archxerciser (Elginex Corporation, Lombard, Illinois, USA) to strengthen toe plantarflexor muscles..

(iv) *Falls prevention education*: the booklet "Don't fall for it. Falls can be prevented!" subsidised by the Commonwealth Department of Health and Ageing will be provided. This booklet provides a general overview of risk factors for falls and outlines strategies to prevent falls, including regular eye checks, medication assessment, household hazard assessment and general exercise guidelines.

### Baseline assessments

Demographic data will be collected at baseline and will include age, gender, height, weight, country of birth, education, source of income, falls history, eye problems, health conditions, medications, walking aids, use of community services, foot problems, foot posture and use of podiatry services. The *Active Australia *survey questionnaire will be used to obtain a baseline measurement of the physical activity levels of the participants [42].

### Primary outcome measures

All participants will be followed for 12 months following baseline assessment to record the number of falls. Falls, defined as "an unexpected event in which the participant comes to rest on the ground, floor, or lower level" [43] will be monitored using monthly mail-out calendars. When a fall occurs, specific details about fall injuries will be obtained through structured telephone interviews. If falls calendars are not returned at the end of each month, research staff will contact the participants by telephone to obtain the missing data. Consistent with the recommendations of the Prevention of Falls Network Europe group, three falls outcomes will be used as the primary outcomes: the number of fallers, the number of multiple fallers and the falls rate. As a safety measure, the time to first fall will be recorded as a secondary measure to reflect adverse events from the intervention [43].

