### Secondary outcome measures

All participants will be assessed at baseline and at six months by an assessor blinded to group allocation. The secondary outcome measures include:

(i) *Foot pain*: the Manchester Foot Pain and Disability Index (MFPDI) will be used to assess foot pain [39]. The MFPDI consists of 19 statements prefaced by the phrase "Because of pain in my feet", formalised under three constructs: functional limitation (10 items), pain intensity (five items), and personal appearance (two items), with three possible answers: "none of the time" (score = 0), "some days" (score = 1), and "most days/every day" (score = 2). The last two items are concerned with difficulties in performing work or leisure activities, which are omitted if the respondent is of retirement age. The total score (range: 0 to 34) will be used to measure the degree of improvement in foot pain. The MFPDI has been shown to be a suitable tool for assessing foot pain in the older population [44], has high construct validity and has been shown to be sensitive to improvement following a self-management intervention [45].

(ii) *Physiological falls risk*: changes in physiological falls risk will be assessed using the Physiological Profile Assessment (PPA) [5]. Based on the performance of five physiological domains (vision, proprioception, strength, reaction time and balance), the PPA computes a falls risk score (standardised score) for each individual; this measure has a 75% predictive accuracy for falls in older people [46]. The five assessment items (Figure 5) are a test of vision (edge contrast sensitivity using the Melbourne Edge test), peripheral sensation (lower limb proprioception), lower limb strength (knee extension strength), reaction time using a finger press as the response, and body sway (sway when standing on a medium density foam rubber mat). Details regarding each of these tests are provided elsewhere [5]. Several studies have reported significant improvements in PPA scores following exercise interventions [47,48].

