### Statistical analysis

Statistical analysis will be undertaken using SPSS version 14.0 (SPSS Corp, Chicago, Ill, USA) and STATA 8 (Stata Corp, College Station, Tex., USA) statistical software. All analyses will be conducted on an intention-to-treat principle using all randomised participants [69]. Missing data will be replaced with the last score carried forward. Demographic characteristics and baseline data will be summarised by descriptive statistics. Consistent with the recommendations of the Prevention of Falls Network Europe group [43], three falls outcomes will be used as the primary outcomes: the number of fallers, the number of multiple fallers and the falls rate. The number of fallers and multiple fallers (two or more falls) will be compared by calculating relative risks. The number of falls and falls rate per person per year in the two groups will then be compared using negative binomial regression models. This approach takes into account all falls and adjusts for varying duration of follow-up [70,71]. The continuously-scored secondary outcome measures at baseline and the six month follow-up appointments will be compared using analysis of covariance with baseline scores and intervention group entered as independent variables [72,73].

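### The only measure labelled as safety, time to first fall, largely restates the faller outcome and can show only fall-type harm

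*Protocol article*

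**What the plan says.** The Primary outcome measures section of the protocol article fixes the following:

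- Follow-up: "All participants will be followed for 12 months following baseline assessment to record the number of falls".
- Source: falls "will be monitored using monthly mail-out calendars".
- Efficacy: "three falls outcomes will be used as the primary outcomes: the number of fallers, the number of multiple fallers and the falls rate".
- Safety: "As a safety measure, the time to first fall will be recorded as a secondary measure to reflect adverse events from the intervention".
- Injuries: "When a fall occurs, specific details about fall injuries will be obtained through structured telephone interviews".

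No other measure in the article carries a safety label. The Secondary outcome measures section adds foot pain on the Manchester Foot Pain and Disability Index (MFPDI) at baseline and six months: "The total score (range: 0 to 34) will be used to measure the degree of improvement in foot pain". The Intervention group section describes footwear advice with a purchase voucher, customised insoles, and home exercise three times a week for six months. Telephone calls at weeks 1, 4, 12 and 20 are part of the exercise programme and are meant to support adherence.

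**The concern.** The article is not silent on safety. It names one measure and says what that measure is for, and the measure fits that purpose only in part. It is built from the event the trial aims to prevent, so if the intervention prevents falls, the safety measure will tend to look favourable for that reason alone.

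The package puts insoles and new shoes on feet that are already painful and adds regular foot and ankle exercise. Besides falls, its plausible harms include skin lesions or blisters, new or worse foot or leg pain, and exercise strain. None of these enters a time to first fall unless the participant also falls. A safety statement resting on this measure would therefore cover falls and nothing else, for a package that the article hopes to see generalised to clinical practice.

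**Working it through.** **1. Overlap by definition.** The safety measure and the faller outcome use the same fall definition, the same calendars and the same 12 months. A first-fall time is observed if and only if the participant is a faller. The safety measure adds only when the first fall happened.

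**2. Overlap in numbers.** Inputs from Sample size: 60% fallers in control, 42% in intervention, alpha 0.05, 80% power, 15% drop-out, 143 per group, recruitment of 150 per group. Assumptions: two-sided alpha and a constant first-fall hazard.

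- The article's own figure: the two-proportion formula with pooled variance and no continuity correction gives 120 per group. Dividing by 1 − 0.15 gives 142, against the stated 143. The inputs are thus read as intended.
- Implied hazard ratio: ln(1 − 0.42) / ln(1 − 0.60) = ln 0.58 / ln 0.40 = 0.594.
- Evaluable per arm: 150 × 0.85 = 127.5. Expected first falls: 127.5 × (0.60 + 0.42) = 130.
- Power for time to first fall (Schoenfeld): Φ(√(130/4) × |ln 0.594| − 1.96) = Φ(1.0) = 84%.
- Power for the proportion of fallers at 127.5 per arm: 82%.
- Simulation (128 per arm, 4,000 runs, censoring at 12 months): the log-rank and two-proportion statistics correlate at 0.97 with no effect and 0.98 with the planned effect.
- Harmful direction in the same simulation: with no effect, the log-rank statistic exceeded 1.96 against the intervention in 2.7% of runs, about the nominal rate. The measure is therefore free to move towards harm.

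**3. What each source can show.**

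| Source | Arms | Timing | Harm without a fall |
|---|---|---|---|
| Time to first fall | both | 12 months | none |
| Fall-injury interview | both | after a fall only | none |
| MFPDI total | both | baseline and six months | foot pain only, as a score; no skin lesions or strain as events |
| Adherence calls | intervention | weeks 1 to 20 | no adverse-event question mentioned; not symmetric |

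Only the first row is designated as safety.

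**4. What a direct question would detect.** The article gives no harm rates, so 1% and 2% are assumptions. The chance of seeing at least one case among n treated participants is 1 − (1 − p)^n.

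| Assumed harm rate p | n = 150 | n = 127 (after 15% drop-out) |
|---|---|---|
| 2% | 95% | 92% |
| 1% | 78% | 72% |

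Time to first fall would register none of these cases unless the participant also fell.

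**The case against.** Several points on the other side are sound and limit the finding.

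- A reader might infer that the measure cannot show any harm. That is not so. The Background links footwear features to balance and falls, so falls caused by new shoes, insoles or exercise are a real possible harm. An excess of earlier falls would appear, and would show better here than in the 12-month proportion. The near-unit correlation above assumes a constant hazard and would weaken if the excess were confined to the early months.
- A reader might infer that falls after the first are lost. They are not: multiple fallers and the falls rate are primary outcomes, and the negative binomial model uses every fall.
- A reader might infer that the planned analyses mishandle a censored time. The relevant sentence reads: "The continuously-scored secondary outcome measures at baseline and the six month follow-up appointments will be compared using analysis of covariance". It does not claim to cover time to first fall, and a method for one secondary measure is ordinarily left to the analysis plan.
- A reader might infer that the trial collects no adverse events. The article cannot establish this. It condenses a full protocol that is not shown and that may contain an adverse-event procedure.
- Worse foot pain is not wholly invisible. A blinded assessor takes the MFPDI in both arms and the score can rise as well as fall; the SF-12 physical score also bears on harm.

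The article cites consensus recommendations on falls outcomes for its choice. What they say about this measure cannot be checked here, and nothing in this point depends on it.

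What remains is the sentence as written. A fuller procedure elsewhere would not make time to first fall a measure of non-fall harm. The MFPDI total at a single follow-up visit would miss transient skin injury and anything after month six, and a group mean can improve while some participants are harmed.

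**Conclusion.** The point holds in a limited form. The one measure labelled as safety is nearly the same comparison as the proportion of fallers: power 84% against 82%, with test statistics correlated at 0.97 to 0.98. It informs on fall-type harm only. These figures rest on the article's 60% and 42%, two-sided alpha, a constant hazard and 15% loss in each arm.

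The defect lies in the property claimed for the measure and in the harms it leaves uncovered. It touches neither the primary comparison nor the sample size. It should still be corrected, because a favourable result on this measure could be read as evidence that the whole package is safe.

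**What to change.** 1. Describe time to first fall as a secondary fall outcome that reflects fall-type harm only.
2. Add a short adverse-event item to the monthly calendar already sent to both arms: skin lesion or blister, new or worse foot or leg pain, exercise-related injury.
3. Report the number of events and of participants affected, by arm, in one descriptive table.
4. If the full protocol already collects these harms in both arms, name that collection as the safety measure in place of step 2.

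Using the calendar rather than the adherence calls keeps ascertainment the same in both arms. The cost is one extra item on an existing form, one table, and slightly more participant burden and data entry. The sample size and primary analyses stay as they are.
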